#### Secondary qualitative objectives

We also aim to explore the profiles of participants who refuse to participate, who are non-adherent to the intervention programs and who also who adhere fully to the programs in order to decipher the role played by physical, environmental, sociological and psychological factors from a transdisciplinary perspective. The objective will be to obtain a better understanding of adherence to physical activity interventions and recommendations and to identify potential factors which were not identified in the quantitative analysis. For this purpose, we aim to:

Examine the links made by participants who are non-adherent regarding the different factors associated with non-adherence to physical activity. Understand how these individuals explain these situations on the basis of their personal situation, their representation of health and/or their understanding of the impact of physical activity on health.Understand how these individuals explain these situations, in regard to the program adherence, on the basis of their personal situation, their representation of health and/or their understanding of the impact of physical activity on health.For adherent patients, to explore the factors which are associated with the success to the program.To understand the interactions between patients and healthcare professional in the conduct of the program and the success or failure.

#### Secondary qualitative outcome measures

Criteria will come from the analyses of semi-structured qualitative interviews conducted separately with participants and healthcare professional. These interviews will explore participants’ experience with physical activity and exercise, motivation to perform physical activity, beliefs that exercise will improve health, factors that limit their ability to engage in exercise, and the importance of self-regulation in exercise adherence.

#### Implementability of the intervention

The criteria of acceptability, fidelity, and feasibility are evaluated according to the analytical framework of Klaic et al. [44]. Acceptability, that is, the extent to which the individuals who deliver or receive the intervention consider it appropriate, will be assessed using the following indicators: the number of study dropouts, participant satisfaction; and adverse effects reported by professionals and participants.

Fidelity, understood as the strategies used to control and improve the reliability and validity of the intervention, will be evaluated using the following indicators: the fidelity of the intervention to participants’ expectations; responsiveness to participants’ needs; the quality of interpersonal behaviors of professionals as perceived by participants, assessed with the Interpersonal Behavior Questionnaire (IBQ).

Feasibility will be assessed based participant adherence to the intervention, i.e., the number of individuals attending the scheduled sessions, will be recorded, along with the reasons for non-adherence as reported by participants to the coordinator.

### Sample size calculations

Sample size and power calculations were performed using R statistical software under the following assumptions: balanced randomization (1:1:1 across the three arms); changes in steps per day follow a Gaussian distribution, centered at 0 in the control arm, 1800 in the lifestyle intervention arm, and 2200 in the lifestyle and sleep intervention arm, with a standard deviation of 2121 [45, 46]; changes in EQ-5D-5 L scores follow a Gaussian distribution, centered at 0 in the control arm, 0.07 in the lifestyle intervention arm, and 0.14 in the lifestyle and sleep intervention arm [47], with a standard deviation of 0.21. This 0.07 increase is based on the anticipated observation of a minimal important difference to infer changes in health-related quality of life [48].

Based on these assumptions, a sample of 181 participants provides > 90% power to detect the following three primary objectives:

(i)superiority of the lifestyle arm versus control for steps per day;(ii)superiority of the lifestyle + sleep arm versus control for steps per day;(iii)superiority of the lifestyle + sleep arm versus control for EQ-5D-5 L.

This design also provides reasonable power for two additional comparisons:

(iv)lifestyle versus control for EQ-5D-5 L;(v)lifestyle + sleep versus lifestyle for EQ-5D-5 L.

Accounting for an anticipated 10% dropout rate, the study will aim to recruit 201 participants.

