#### Analysis of the outcomes

The primary objectives consist in 5 different questions, which are organized in a single hierarchy (see Figure S1) so as to control the overall type I error of the primary objectives at a 5% level. Therefore, to avoid the inflation of alpha risk associated with multiple tests, the next level of the hierarchy will only be tested if the null hypothesis of the previous level is rejected. Primary and secondary outcomes (continuous variables) will be compared between groups using a t-test. Mixed effects linear models will also be used when necessary (repeated measures). The significance level of all tests corresponding to secondary objectives will be set at 0.05. Analyses will be conducted using R software or SAS.

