## Discussion

To our knowledge, this is the first fully powered trial to investigate the effectiveness of a lifestyle intervention integrating sleep, physical activity, and diet on quality of life and physical activity levels in inactive adults. This study builds on previous research that has demonstrated the individual benefits of physical activity and diet interventions, but has yet to examine the combined impact of these factors alongside sleep improvement in this population.

The SPIRAL+ study aims to fill significant gaps in the existing evidence on lifestyle interventions. While there is substantial research on the individual effects of physical activity, diet, and sleep, there is limited evidence on how a multi-component intervention targeting all three behaviors may work together to improve long-term health outcomes in inactive adults. By including a sleep component, this study addresses the critical need for interventions that focus on improving sleep quality, which is often overlooked despite its significant role in overall health and well-being.

A notable strength of this trial is its longitudinal design, with assessments at both 6 and 12 months. The 6-month timepoint allows us to evaluate the immediate effectiveness of the intervention, while the 12-month follow-up provides insight into the sustainability of behavioral changes and their long-term impact on health outcomes. This extended follow-up is particularly important given that maintaining improvements in physical activity, diet, and sleep remains a major challenge in lifestyle interventions.

Methodologically, the study combines objective and subjective assessments of both physical activity and sleep, providing a comprehensive evaluation of the intervention’s impact. Similarly, the addition of validated questionnaires offers insights into diet, mental wellbeing, and motivational processes, capturing psychological and behavioral dimensions that may explain adherence and maintenance. The qualitative component further strengthens the study by exploring barriers and facilitators to engagement, which may inform strategies to enhance scalability and real-world implementation.

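### The two EQ-5D-5L comparisons described as reasonably powered each have about 44% power, and the sleep comparison has about 12% if it is tested last in the hierarchy

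*Protocol article*

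**What the plan says.** Under Sample size calculations, the EQ-5D-5L changes are taken to be "centered at 0 in the control arm, 0.07 in the lifestyle intervention arm, and 0.14 in the lifestyle and sleep intervention arm". Their SD is put at 0.21. The article then states that "a sample of 181 participants provides > 90% power to detect the following three primary objectives": (i) lifestyle versus control on steps, (ii) lifestyle + sleep versus control on steps, and (iii) lifestyle + sleep versus control on EQ-5D-5L. For (iv) lifestyle versus control and (v) lifestyle + sleep versus lifestyle, both on EQ-5D-5L, it says only: "This design also provides reasonable power for two additional comparisons".

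Under Analysis of the outcomes, all five count as primary questions in a single hierarchy at an overall 5% level, where "the next level of the hierarchy will only be tested if the null hypothesis of the previous level is rejected". The comparisons use a t-test. The order of the hierarchy is given in Figure S1, which is not available here.

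Study objectives makes the added value of the sleep component, compared with the lifestyle program without it, the primary objective. The Discussion says that, to the authors' knowledge, "this is the first fully powered trial to investigate the effectiveness of a lifestyle intervention integrating sleep, physical activity, and diet".

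**The concern.** A number is given for the three comparisons where power is high, and only an adjective for the two where the assumed difference is half as large. Halving the difference from 0.14 to 0.07 at the same SD and sample size costs a great deal of power, so the adjective needed checking.

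Comparison (v) is the only one of the five primary questions that sets lifestyle + sleep against lifestyle; none of the five does so for steps. If its power is low, a non-significant result is likely even when sleep adds exactly the benefit assumed. A reader told that power was reasonable, or that the trial was fully powered, could then take that result as evidence that sleep adds nothing.

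**Working it through.** **Inputs.** From Sample size calculations: N = 181 evaluable, allocated 1:1:1, so n = 181/3 = 60.3 per arm; EQ-5D-5L mean changes 0, 0.07 and 0.14, SD 0.21; step changes "centered at 0 in the control arm, 1800 in the lifestyle intervention arm, and 2200 in the lifestyle and sleep intervention arm", SD 2121. From Analysis of the outcomes: t-test, 5% level. Sidedness is not stated, so two-sided is assumed and one-sided is shown as a variant.

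**Formula.** With d = difference/SD, normal-approximation power = Φ(d·√(n/2) − 1.96), where √(60.3/2) = 5.49. The noncentral t gives the t-test figure.

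| Comparison | d | d·√(n/2) | Power, normal | Power, t-test |
|---|---|---|---|---|
| (i) | 1800/2121 = 0.849 | 4.66 | 99.7% | 99.6% |
| (ii) | 2200/2121 = 1.037 | 5.70 | 99.99% | 99.99% |
| (iii) | 0.14/0.21 = 0.667 | 3.66 | 95.6% | 95.3% |
| (iv) | 0.07/0.21 = 0.333 | 1.83 | 44.9% | 44.3% |
| (v) | (0.14 − 0.07)/0.21 = 0.333 | 1.83 | 44.9% | 44.3% |

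The stated power above 90% is reproduced for (i) to (iii), jointly about 95%. Recruitment also agrees: 181/0.9 = 201.1, stated as 201. Only the description of (iv) and (v) fails.

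**Hierarchy.** The estimates for (iv) and (v) are (L − C) and (LS − L), where C, L and LS are the control, lifestyle and lifestyle + sleep means. Their covariance is −Var(L) = −σ²/n and each has variance 2σ²/n, so their correlation is −0.5. When one is high, the other tends to be low. The probability that both are significant is 12.0% from a bivariate normal with that correlation. Assuming independence, 0.44 × 0.44 = 19% would overstate it.

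Simulating all five t-tests (400,000 replicates, arms of 60 or 61, correlation between steps and EQ-5D-5L of 0, 0.3 or 0.6) gives:

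- (i) to (iii) all rejected: about 95%
- (i) to (iv) all rejected: about 44%
- all five rejected: 11.5% to 12.0%, whatever the order of testing
- (v) rejected when placed directly after (iii): about 44%

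**Precision of (v).** At 60 per arm the standard error is 0.21 × √(2/60) = 0.0383. The expected 95% confidence interval half-width is 1.98 × 0.0383 = 0.076, wider than the 0.07 to be detected. The difference detectable with 80% power is about (1.98 + 0.845) × 0.0383 = 0.108.

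**Variants.**

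| Variant | (iv) or (v) alone | (v) tested last |
|---|---|---|
| Two-sided 5%, N = 181 | 44% | 12% |
| Two-sided 5%, all 201 analysed | 48% | 15% |
| One-sided 5%, N = 181 | 57% | 25% |

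For 80% power the trial would need n = 2 × (1.96 + 0.842)² × (0.21/0.07)² = 141.3, so 142 evaluable per arm (426 in all), or an SD of about 0.137 instead of 0.21 at N = 181.

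**The case against.** The strongest reply is that the article already separates two tiers. It claims high power for three comparisons and uses a weaker, unquantified word for the two it calls additional, so no stated number is wrong. That is true, but Analysis of the outcomes counts all five as primary, and one of the two carries the stated primary objective. A test with 44% power under the plan's own assumptions is not reasonably powered.

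Second, the testing order is in Figure S1, which is not shown, and sidedness is not stated. Both points stand as conditions. If (v) follows (iii) directly, it keeps about 44%. If testing is one-sided at 5%, (v) alone has 57%, so rejection would then be the likelier outcome for that test taken alone. Neither reading comes near 80%, and under two-sided testing the 12% for rejecting all five does not depend on the order.

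Third, the claim might mean that at least one of (iv) and (v) succeeds, which with (i) to (iii) has a probability of about 76%. But the sentence claims power for both comparisons, and a fixed sequence gives no credit for either-or success.

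Fourth, lifestyle + sleep can also be compared with lifestyle on secondary outcomes. That is correct, so the point is limited to the five primary questions.

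Finally, the Discussion's claim of full power sits in a general sentence about novelty that names no comparison. It is the lesser part of the problem, but it describes a trial whose primary objective rests on (v).

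**Conclusion.** The concern holds. On the article's own inputs, with a two-sided 5% t-test and 181 evaluable participants, power is about 44% for (iv) and for (v). The chance of rejecting all five primary hypotheses is about 12%, and that is the power for (v) if it is tested last. Under two-sided testing, a non-significant (v) is more likely than a significant one even if every planning assumption is true. The 44% does not depend on the order of the hierarchy; the 12% for (v) does. One-sided testing at 5% raises the two figures to 57% and 25%, which does not rescue the claim. The power stated for (i) to (iii) is correct.

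**What to change.** 1. In Sample size calculations, replace the adjective with figures: about 44% for (iv) and for (v) taken alone (two-sided 5%), and about 12% for (v) if it is tested after (iv). Match the sequential figure to the order in Figure S1 and name the sidedness.
2. Give the expected 95% confidence interval half-width for (v), 0.076, beside the assumed difference of 0.07.
3. In the Discussion, delete the claim of full power or limit it to (i) to (iii).
4. State that a non-significant (v) will be reported as inconclusive, with its confidence interval, and not as absence of an effect of the sleep component.

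These are changes of wording only. They need no extra participants and no change of design; the cost is that the stated power looks less favourable.

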### Data analysis

The full statistical analysis plan will be validated before the database is locked, which will be performed according to the RCDMS.MOP.009 operating procedure of the CHU Grenoble Alpes, after the usual data management procedure and according to the specifications defined a priori. The general approach of the data analysis is described below:

Outcomes will be compared between groups following the intention-to-treat (ITT) principle, i.e. all patients will be analyzed in the group they were initially allocated to. However, this implies obtaining complete data for all randomized patients, which in practice is rarely possible. For the main analysis, we propose an analysis on the modified ITT population (mITT), which will include patients for whom the following protocol deviations will be observed:

Patients assigned to an intervention group who finally did not receive the (or received incomplete) intervention, whatever the reason, but who completed follow-up, will be analyzed in the corresponding intervention group;Patients allocated to the control group who would benefit from another intervention will be analyzed in the control group;

In addition, we propose the following two sensitivity analyses. First, an analysis on the ITT population, i.e. including patients who did not complete follow-up. This implies missing data imputation. Multiple imputation methods will be used, provided the assumption that the data are missing at random (MAR) is credible [49, 50]. If the ‘missing not at random’ (MNAR) hypothesis cannot reasonably be excluded, different sensitivity analyses (best-worst and worst-best) will be implemented to estimate the extent of the uncertainty associated with these missing data. Second, an analysis on the per protocol population, i.e. patients who actually received the treatment as initially allocated, and who completed follow-up.

The characteristics of the study population at inclusion will be presented by the mean and standard deviation for continuous variables (or by the median and interquartile range, depending on their distribution); and by their frequency and percentage for categorical variables.

#### Analysis of the outcomes

The primary objectives consist in 5 different questions, which are organized in a single hierarchy (see Figure S1) so as to control the overall type I error of the primary objectives at a 5% level. Therefore, to avoid the inflation of alpha risk associated with multiple tests, the next level of the hierarchy will only be tested if the null hypothesis of the previous level is rejected. Primary and secondary outcomes (continuous variables) will be compared between groups using a t-test. Mixed effects linear models will also be used when necessary (repeated measures). The significance level of all tests corresponding to secondary objectives will be set at 0.05. Analyses will be conducted using R software or SAS.

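### Read in the listed order, the hierarchy tests the sleep comparison on EQ-5D-5L only after lifestyle versus control; testing the two in parallel after (iii) would lift its chance of success from about 12% to 43% at no cost in type I error

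*Protocol article*

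**What the plan says.** In the protocol article, *Analysis of the outcomes* describes the five primary questions as "organized in a single hierarchy (see Figure S1"). The stated aim is a family-wise error of 5% across the five. The rule is that "the next level of the hierarchy will only be tested if the null hypothesis of the previous level is rejected". Continuous outcomes "will be compared between groups using a t-test"; the text does not say whether the tests are one- or two-sided.

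The questions themselves are numbered in *Sample size calculations*. Questions (i) and (ii) compare each intervention arm with control on steps, and (iii) compares lifestyle + sleep with control on EQ-5D-5L. Two further comparisons follow: "iv)lifestyle versus control for EQ-5D-5 L;(v)lifestyle + sleep versus lifestyle for EQ-5D-5 L". The first three are given more than 90% power with 181 participants. The last two are credited with reasonable power, without a figure.

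The assumed EQ-5D-5L changes are "centered at 0 in the control arm, 0.07 in the lifestyle intervention arm, and 0.14 in the lifestyle and sleep intervention arm". Their assumed SD is 0.21.

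*Study objectives* makes the added value of the sleep component over the lifestyle programme alone the primary objective.

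**The concern.** Of the five questions, only (v) sets lifestyle + sleep against lifestyle, so only (v) bears on the primary objective, and then only for quality of life. On the serial reading it stands last, behind a comparison that does not involve sleep and has less than even odds of succeeding under the plan's assumptions.

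The gate also works against (v). The lifestyle arm is the treated arm in (iv) and the reference arm in (v), so a high lifestyle mean opens the gate and at the same time shrinks the difference that (v) has to show. If the lifestyle programme alone does little for quality of life and sleep does most of the work, (iv) will usually fail and the sleep effect will not be tested at all.

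The gate's stated purpose is to avoid alpha inflation. Between (iv) and (v) it is not needed for that.

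**Working it through.** **Inputs** (all from *Sample size calculations*): EQ-5D-5L mean changes 0 / 0.07 / 0.14, SD 0.21; step changes 0 / 1800 / 2200, SD 2121; 1:1:1 allocation; 181 evaluable, so about 60 per arm. Assumptions: two-sided 5% tests, with one-sided 5% as the range, and steps and EQ-5D-5L uncorrelated (correlations of 0.3 and 0.5 change nothing material).

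**1. The plan's own figure.** Approximate power is Φ(δ / (σ√(2/n)) − 1.96), with n = 60 and √(2/60) = 0.1826.
- (i): 1800 / (2121 × 0.1826) = 4.65, power 99.6%.
- (ii): 2200 / (2121 × 0.1826) = 5.68, power 99.99%.
- (iii): 0.14 / (0.21 × 0.1826) = 3.65, power 95.5% (noncentral t: 95.2%).
- All three jointly, by simulation: 94.8%.

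The stated power above 90% is reproduced. 181 / 0.9 = 201.1 agrees with the 201 to be recruited.

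**2. Questions (iv) and (v) taken singly.** Both differences are 0.07. 0.07 / (0.21 × 0.1826) = 1.826 and Φ(1.826 − 1.960) = 44.7% (noncentral t: 44.1%).

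**3. Their dependence.** The lifestyle mean enters the two statistics with opposite sign, so their correlation is −(σ²/n) / (2σ²/n) = −0.5. Two independent tests would both succeed with probability 0.441 × 0.441 = 19.4%. With correlation −0.5 the bivariate normal gives 11.8%.

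**4. The two rules compared** (400,000 simulated trials, shared arms, pairwise t-tests, all gates applied).

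| Setting | (v) confirmed, serial | (v) confirmed, parallel after (iii) |
|---|---|---|
| Plan's assumptions, two-sided 5% | 11.6% | 43.4% |
| Plan's assumptions, one-sided 5% | 24.4% | 56.3% |
| 67 per arm (no dropout), two-sided | 15.2% | 47.8% |
| EQ-5D-5L 0 / 0.035 / 0.14, two-sided | 7.4% | 75.4% |
| EQ-5D-5L 0 / 0 / 0.14, two-sided | 3.6% | 91.1% |

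In the first row, (iv) is reached and rejected in about 43.5% of trials under either rule. Once it is rejected under the serial rule, (v) succeeds in only 26.6%: 0.435 × 0.266 = 11.6%. Under the parallel rule at least one of (iv) and (v) succeeds in about 75%. The relative loss for (v) is 1 − 11.6/43.4 = 73% two-sided and 1 − 24.4/56.3 = 57% one-sided.

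**5. Type I error of the parallel step.**
- If any of (i) to (iii) is a true null, any false rejection requires rejecting the first true one in the sequence, which happens with probability at most 5%.
- If (i) to (iii) are all false, lifestyle + sleep differs from control on EQ-5D-5L. Lifestyle = control and lifestyle + sleep = lifestyle cannot then both hold, because together they imply lifestyle + sleep = control. At most one true null remains, and it is tested at 5%.
- The same logic holds for one-sided nulls.

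Simulated family-wise error across the null configurations tried ran from 2.4% to 5.06%, which is compatible with the 5% bound given Monte Carlo error.

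**The case against.** The strongest objection is that the article does not actually state the serial order of (iv) and (v). It leaves the structure to Figure S1, which is not available here, and it gates by level without saying that there are five levels. The (i) to (v) numbering comes from the sample size section, which groups comparisons by power and never calls the list a testing order. Questions (iv) and (v) are introduced together with one shared remark on power, which would fit a shared last level. This stands as a condition on the finding. On the other side, the wording of a single hierarchy and the singular null hypothesis of the previous level favour the serial reading.

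A second objection is that a fixed sequence is a valid procedure. That also stands. A reader might infer that the plan fails to control its type I error; it does not. The serial rule meets the stated 5% and only gives away power.

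A third is that the remedy leaves (v) more likely to fail than to succeed. This is true, and the low power of (v) against the stated objective is a separate matter that changing the order cannot cure.

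**Conclusion.** The point holds in conditional form. If (iv) gates (v), as the text and numbering suggest, the only question that addresses the primary objective is confirmed in about 11.6% of trials, where about 43.4% is available at the same sample size and the same error rate (one-sided: 24.4% against 56.3%). This rests on the plan's means and SDs, about 60 evaluable per arm, and the listed order. The gain is larger if lifestyle alone does less for EQ-5D-5L than assumed.

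Two stronger readings are not supported. It cannot be asserted that the plan is strictly serial, because Figure S1 might already put (iv) and (v) on one level, in which case there is no loss. Nor would the change make (v) well powered: it would stay at roughly 43% to 45%.

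**What to change.** By a dated, justified amendment before database lock, write the hierarchy as (i), then (ii), then (iii), then (iv) and (v) in parallel, each at 5%. Cite the logical restriction among the three pairwise EQ-5D-5L nulls, state whether the tests are one- or two-sided, and align Figure S1. If Figure S1 already shows (iv) and (v) on one level, a sentence in the text saying so is enough.

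The change costs no participants, no type I error and no power for (iv). It does alter the confirmatory hierarchy of a trial that began recruiting in May 2024, so the amendment should record when and why it was made. *Data analysis* has the full analysis plan validated before database lock, which gives a route for it.

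Two limits apply. A single sequence with (v) ahead of (iv) is not a free alternative: the two assumed differences are equal, so by symmetry power for (iv) would fall to about 11.6%. And lifestyle + sleep against lifestyle on steps should not be added to the parallel step, because the restriction among the EQ-5D-5L nulls does not cover it.

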### Outcomes

#### Primary outcome

The study has two primary outcomes, assessed 6 months after randomization:Steps per day, measured objectively using an Actigraph GT3X accelerometer (Actigraph Corp, USA). Steps per day were chosen because increases in daily step count are strongly associated with reduced all-cause mortality [31]. Furthermore, step count is passively tracked by widely used consumer technologies (e.g., smartphones), giving it practical relevance. Recent dose–response evidence also provides insights to inform future physical activity guidelines [32].Health-related quality of life, measured with the EQ-5D-5L questionnaire. This instrument is a widely used, cognitively simple, self-administered measure that assesses five dimensions of health (mobility, self-care, usual activities, pain/discomfort, anxiety/depression), each rated on five severity levels, along with a visual analog scale (EQ-VAS) for overall health [33]. Quality of life was selected as a co-primary outcome because self-rated health and health-related quality of life are robust predictors of mortality and chronic disease risk, and are sensitive to changes in lifestyle behaviors.

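### The primary comparison is a t-test with no baseline covariate and no stated scale; a baseline-adjusted model would be at least as precise at no cost, though the gain is modest

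*Protocol article*

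**What the plan says.** The Analysis of the outcomes section of the Protocol article fixes the test: "Primary and secondary outcomes (continuous variables) will be compared between groups using a t-test". Mixed models are mentioned only for repeated measures, with no baseline term. Five questions sit in one hierarchy "so as to control the overall type I error of the primary objectives at a 5% level".

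The scale is not stated there. The Primary outcome section says "The study has two primary outcomes, assessed 6 months after randomization". The Sample size calculations section works with changes: "changes in steps per day follow a Gaussian distribution, centered at 0 in the control arm" (then "1800 in the lifestyle intervention arm, and 2200 in the lifestyle and sleep intervention arm", SD 2121), and "changes in EQ-5D-5 L scores follow a Gaussian distribution, centered at 0 in the control arm", then "0.07 in the lifestyle intervention arm, and 0.14 in the lifestyle and sleep intervention arm [47], with a standard deviation of 0.21". It claims more than 90% power for (i)-(iii) with 181 participants. For (iv), lifestyle versus control, and (v), lifestyle plus sleep versus lifestyle, both on EQ-5D-5L, it describes the power in words only.

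Both primary variables are measured at baseline (Table 2). The Randomization procedure section places allocation after the baseline assessment, and the non-inclusion criteria already require a baseline EQ-5D-5L.

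**The concern.** A t-test on final values fixes the baseline coefficient at 0, and a t-test on change fixes it at 1. ANCOVA estimates it, so apart from one degree of freedom its residual variance is no larger than either. The plan therefore chooses a method that can lose precision and cannot usefully gain any, although the covariate is in hand. Because the scale is not fixed, the loss could be small or substantial.

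The comparison with most to gain is (v). The Study objectives section asks whether adding sleep support improves on the lifestyle programme alone, and (v) is the only one of the five contrasts that addresses this. It is also, with (iv), one of the two weakest.

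**Working it through.** **Inputs (Sample size calculations).** 181 evaluable in three equal arms, so n = 181/3 = 60.33 per arm. Steps: differences from control 1800 and 2200, SD 2121. EQ-5D-5L: differences 0.14 for (iii) and 0.07 for (iv) and (v), SD of change 0.21.

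**Assumptions.** Two-sided 5% (sidedness is not stated); equal variance at baseline and 6 months; baseline-to-6-month correlation ρ, which the document does not give, so a range is shown.

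**Formula.** SE = SD × √(2/n), with √(2/60.33) = 0.1821. Power = Φ(difference/SE − 1.96).

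**The plan's own figures reproduce on the change scale.**
- (i): SE = 2121 × 0.1821 = 386; 1800/386 = 4.66; power 99.6%.
- (ii): 2200/386 = 5.70; power above 99.9%.
- (iii): SE = 0.21 × 0.1821 = 0.0382; 0.14/0.0382 = 3.66; power 95.6%.
- Recruitment: 181/0.9 = 201.1, against 201 stated.

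**Contrasts (iv) and (v), change-score t-test.** 0.07/0.0382 = 1.83; Φ(1.83 − 1.96) = 45%. The noncentral t gives 44%. One-sided it would be 57%.

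**Alternatives.** Let σ be the SD at a single visit.
- Var(change) = 2σ²(1 − ρ).
- ANCOVA residual variance = σ²(1 − ρ²), which is (1 + ρ)/2 of the change variance. ANCOVA SD = 0.21 × √((1 + ρ)/2).
- Raw 6-month SD = σ = 0.21/√(2(1 − ρ)).

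| ρ (assumed) | ANCOVA SD | ANCOVA (iv), (v) | ANCOVA (iii) | Raw 6-month SD | Raw (iv), (v) | Raw (iii) |
|---|---|---|---|---|---|---|
| 0.3 | 0.1693 | 62.2% | 99.5% | 0.1775 | 58.2% | 99.1% |
| 0.5 | 0.1819 | 56.1% | 98.8% | 0.2100 | 44.9% | 95.6% |
| 0.6 | 0.1878 | 53.5% | 98.4% | 0.2348 | 37.4% | 90.6% |
| 0.7 | 0.1936 | 51.0% | 97.8% | 0.2711 | 29.4% | 81.0% |
| 0.8 | 0.1992 | 48.8% | 97.1% | 0.3320 | 21.1% | 63.9% |

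The change-score t-test stays at 44.9% for (iv) and (v) and 95.6% for (iii) in every row, because 0.21 is held as the SD of change.

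**Ceiling of the gain.** At ρ = 0 the ANCOVA SD is 0.21 × √0.5 = 0.1485 and power for (iv) and (v) is 73.5%. No ρ ≥ 0 reaches 80%.

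**Where (iii) drops below 90% on raw values.** 90% power needs difference/SE = 1.960 + 1.282 = 3.242, so SE = 0.14/3.242 = 0.0432 and SD = 0.0432/0.1821 = 0.237. Setting 0.21/√(2(1 − ρ)) = 0.237 gives ρ of about 0.61.

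**The case against.** The strongest reply is that the only section naming a scale works with changes, and a change-score t-test already uses each participant's baseline. It is valid and unbiased under randomisation, and its error rate allows for chance imbalance. On that reading the choice between change score and ANCOVA is one of efficiency, and (i)-(iii) keep their stated power without it. The article also gives only a general approach ahead of a full SAP. Most of this stands. It does not remove the point, because the article positively names the test rather than leaving it open, and the better model needs no further data.

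A reader might infer more than the documents support:
- **That the outcome definition contradicts the sample size section.** It does not. The former gives instruments and a time point; change from baseline to 6 months fits both.
- **That the planning SDs assume zero correlation**, because 2121 and 0.21 are close to √2 times 1500 and 0.15. The article does not say how either SD was derived, so this is numerology without the cited sources.
- **That ANCOVA would lift (iv) and (v) from 44% to 72-83%.** Those figures swap in a single-visit SD of 0.15. At ρ = 0.5 that also makes the SD of change 0.15, so the change-score t-test would already have about 72%. The like-for-like gain to 83% is 11 points.
- **That randomisation is unstratified.** The article describes permuted blocks and mentions no strata; silence in a condensed article does not settle it.

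**Conclusion.** The point holds as a recommended improvement; the planned test is not an error. On the protocol's own basis (0.21 as SD of change, 60.33 per arm, two-sided 5%), baseline adjustment raises power for (iv) and (v) from about 45% to between 49% (ρ = 0.8) and 62% (ρ = 0.3), a gain of about 4 to 17 points. It does not cure their low power, which is a separate sample-size matter.

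The larger risk is the unstated scale. If raw 6-month values were tested, (iv) and (v) would have 29% at ρ = 0.7, and (iii) would miss its stated 90% above ρ of about 0.6. The document does not say that raw values will be used, so this is a reason to fix the wording and not a prediction. The direction of the result is secure; its size depends on ρ and on equal variances at the two visits.

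**What to change.** In the Analysis of the outcomes section, and in the SAP, replace the t-test for both primary outcomes, and for continuous secondary outcomes that have a baseline, with one linear model per outcome: 6-month value on arm (three levels) plus the baseline value of the same variable. Take contrasts (i)-(v) with 95% confidence intervals from these models, tested in the planned hierarchy. Keep the t-test as a supportive analysis and state its scale. ANCOVA also settles the scale question for the primary test, since it gives the same arm contrast whether the response is the 6-month value or the change.

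The cost is about one sentence in each document, with no new data or participants. The Data analysis section says the SAP will be validated before database lock, so the change can still be prespecified. Power for (iv) and (v) should be given as a figure with the assumed correlation, without presenting the adjustment as a remedy for the sample size.
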